## Abstract

**Background:**

Premature ovarian insufficiency (POI), a modifiable cause of infertility with substantial implications for women's well-being, prompts the exploration of efficacious adjunctive treatments. Acupuncture emerges as a promising therapeutic avenue; however, the nuanced effects of acupuncture in POI warrant more comprehensive investigation. The intricate mechanisms dictating individualized responses remain elusive. This trial seeks to assess the effectiveness of acupuncture as an adjunctive treatment for POI, concurrently delving into the impact of transcriptome analysis on peripheral blood to unravel the underpinnings of these individual variations. The overarching objective is to enrich our comprehension of acupuncture's therapeutic potential in the context of POI, with a view to advancing holistic patient care.

**Methods/design:**

Constituting an open-label, nested case-control study, this research endeavors to enroll 108 women diagnosed with POI. Participants will be randomly assigned in a 1:1 ratio to either the study group or the control group, each comprising 54 subjects. Ten patients from each group meeting specific criteria will partake in transcriptome analysis. An additional 10 subjects meeting the study criteria will form a healthy control group. The study group will exclusively undergo acupuncture treatment, while the control group will solely receive Fenmutong. Acupuncture sessions, administered thrice weekly across three menstrual cycles from the fifth day of menstruation, constitute the intervention. Primary outcome measurement rests on Follicle-Stimulating Hormone (FSH) levels, supplemented by secondary assessments encompassing biometric features, hormone biomarkers, anxiety and depression scores, and transcriptome analysis. Baseline measurements precede intervention, with post-intervention evaluations following. The study endeavors to discern specific genes linked to individualized responses to acupuncture. Data analysis, employing SPSS 25.0 software, incorporates a meticulous examination of peripheral blood samples for transcriptome analysis. The investigation aspires to shed light on genetic determinants influencing the effects of acupuncture on women with POI, thereby fostering elevated standards in patient care and management.

**Discussion:**

This study pivots on the principal objective of scrutinizing the efficacy of acupuncture as an adjunctive treatment for POI. Beyond effectiveness, it undertakes an exploration of the intricate mechanisms underlying the diverse responses exhibited by individuals in the context of acupuncture, augmenting the depth of understanding in this therapeutic domain.

## Strengths and limitations of this study

1

This protocol aims to provide patients, clinical practitioners and policy makers with more evidence on the efficacy and safety of acupuncture in the treatment of 108 POIs.

The data extraction and management, assessment of risk of bias sections will be carried out by two or more researchers independently.

The non-inclusion of studies published in languages other than English and Chinese may result in limitations related to publication bias.

Multiple types of acupuncture therapies may increase the risk of heterogeneity.

## Trial Registration

2

China Clinical Trial Registration Centre (No. ChiCTR2300068981). Clinical trial registry by referring to https://www.chictr.org.cn/hvshowproject.html?id=224607&v=1.1.

## Background

3

Premature ovarian insufficiency (POI) has experienced a notable surge in prevalence [1,2], affecting around 6 million Chinese women under 40 years, and emerges as a significant contributor to reproductive disorders and female infertility [3].

Conventional treatments such as hormone replacement therapy (HRT) and Fenmutong, while commonly employed, may yield unsatisfactory outcomes and are associated with notable side effects [4,5]. Consequently, a growing number of POI patients seek complementary and alternative medical (CAM) methods, including acupuncture, reflecting a quest for safer and potentially more effective interventions [6,7].

Acupuncture, a longstanding component of complementary and alternative medicine, has demonstrated promising effects in treating POI [8]. It activates the neural-endocrine-immune network, leading to increased beta-endorphin production, thus influencing the endocrine system and hormones. The appeal of acupuncture lies in its minimal side effects, safety, and cost-effectiveness, potentially addressing the root cause of the condition. Our research team has dedicated considerable effort to studying POI, with previous observations indicating that acupuncture not only alleviate perimenopausal symptoms, restore the menstrual cycle, and regulate serum hormone levels [[9], [10], [11], [12]]. Young patients with relatively good ovarian reserve function appear to experience more favorable treatment outcomes [13]. Conversely, older patients or those with relatively poor ovarian reserve function have also demonstrated improved efficacy with acupuncture therapy for POI, suggesting individual variability as a potential key factor influencing treatment outcomes [14,15]. Despite these observations, the underlying cause of individual response differences to acupuncture in women with POI remains unexplored.

Recent years have witnessed a rise in POI incidence, necessitating an in-depth investigation into its pathogenesis and treatment mechanisms. The advent of transcriptome sequencing technology in 1997 has revolutionized the study of POI's underlying mechanisms. Transcriptome sequencing not only serves as the foundation for identifying new POI-related genes but also facilitates the analysis of immune-related gene regulation, establishing correlations between different genes involved in POI pathogenesis. With approximately 90 genes currently linked to POI, its genetic heterogeneity becomes evident. For instance, studies exposing rats to environmental toxicants and utilizing transcriptome sequencing technology have identified DNA damage repair defects as pivotal in the pathogenesis of POI [[16], [17], [18]].

In this study, our primary objective is to gain a comprehensive understanding of the physiological significance of ovarian dysfunction in POI patients through peripheral blood transcriptome sequencing technology. The interactions between genes and ovarian function play a crucial role in elucidating the association between acupuncture action genes and individual differences observed in ovarian function recovery. To achieve these goals, we have designed a nested case-control study to evaluate the additional benefits of acupuncture treatment for women with POI. Additionally, we aim to investigate the mechanism underlying individual variations in response to acupuncture treatment, utilizing transcriptome gene sequencing analysis on peripheral blood samples. By employing this approach, we aim to systematically explore the potential mechanisms behind the observed individual curative effect differences with acupuncture in women with POI.

Through this research endeavor, we aspire to contribute valuable insights into the therapeutic effects of acupuncture for POI and shed light on the intricate interactions between genes and ovarian function. By understanding the underlying mechanisms, we hope to identify factors influencing the efficacy of acupuncture treatment in women with POI, paving the way for more personalized and effective treatment strategies for this condition. Ultimately, our study aims to contribute to the advancement of knowledge in the field of POI research, potentially improving the quality of life and outcomes for affected individuals.

## Methods/design

4

### Study design

4.1

The proposed investigation adopts an open-label, nested case-control study design to be conducted at Shenzhen Maternity and Child Healthcare Hospital. A total of 108 participants diagnosed with POI will be recruited for the study, and subsequent random assignment will be executed to allocate these patients into either the study group or the control group. The allocation ratio is set at 1:1, ensuring an equal distribution of 54 subjects in each group. Prior to the commencement of any intervention, explicit informed consent will be procured from all participating patients through the endorsement of a consent form administered by the researchers.

Patients comprising the study group will exclusively undergo acupuncture treatment, while those in the control group will exclusively receive Fenmutong. To gain deeper insights into the mechanisms contributing to individual variations in the therapeutic outcomes of acupuncture, a subset of 10 patients from each group will undergo transcriptome analysis. This subset will encompass patients experiencing a serum FSH level decrease of ≥30 % post-acupuncture intervention, alongside those displaying a decrease of <30 % in serum FSH levels following the intervention. The trial's procedural flow is visually represented in Fig. 1, offering a comprehensive overview of the various stages and interventions integral to the study. Additionally, Table 1 provides meticulous details on the data collection process, delineating specific data points and measurements crucial for the comprehensive execution of the research.

**Fig. 1 fig1:**
[figure not shown]
Study flow chart. Note: transcriptome analysis included 10 patients in the POI group and 10 patients in the Fenmutong group, with 5 patients with serum FSH levels ≥30 % and 5 patients with serum FSH levels <30 % in both groups.10 healthy women were selected as the control group.

**Table 1 tbl1:** Overview of study visits.

Itern	Screening visit	Baseline visit	Treatment visit		End of treatment visit
			POI group	Control group	
Sign consent	×				
History	×				×
Biometric features	×	×			×
Transvaginal ultrasound	×	×	×	×	×
Routine test	×				×
hormone biomarkers		×			×
transcriptome analysis		×			×
Questionnaires		×			×
Acupuncture treatment			×		
Adverse events			×		

Note: Participants from the POI group will be selected for transcriptome analysis and will only be assessed at the initial screening visit. History, biometric features, routine test results, and transcriptome analysis will be assessed. Biometric features include body mass index (BMI); transvaginal ultrasound includes endometrial thickness, ovarian volume, antral follicle count, and size of ovarian cysts or developing follicles; Routine tests include blood routine examination, liver function, kidney function, routine stool, and urine tests; Hormone biomarkers include luteinizing hormone (FSH), follicle stimulating hormone (LH), total testosterone, progesterone, estradiol, and leptin; questionnaires include Self-Rating Anxiety Scale (SAS) and Self-Rating Depression Scale (SDS).

### Paticipants recruitment

4.2

This study employs stringent inclusion and exclusion criteria to ensure the selection of participants aligns with the research objectives and mitigates potential confounding factors that could compromise the validity and results of the study.

### Inclusion criteria

4.3

1Participants must meet the diagnostic criteria for POI in accordance with the guidelines outlined in the 2016 edition of the European Society of Human Reproduction and Embryology (ESHRE) document titled " ESHRE Guideline: management of women with premature ovarian insufficiency." [19].2Eligible participants are women aged between 24 and 40 years.3.Control subjects should have no history of reproductive disorders and should exhibit regular menstrual cycles, indicating normal ovarian function, and the Antral Follicle Count (AFC) should generally be between 5 and 12 per side [20].4Women in the POI group should possess Anti-Müllerian Hormone (AMH) values of less than 1.0 ng/ml.5The AFC should be less than 4 for women in the POI group.6All participants must consent to receive treatment according to the study program and willingly commit to being observed throughout the study.7Participants should provide informed consent, demonstrating comprehension of the study procedures, potential risks and benefits, and their voluntary willingness to participate.8Participants must willingly register their case for the study.

Meeting these inclusion criteria ensures the selection of participants capable of contributing valuable data to effectively achieve the research objectives.

### Exclusion criteria

4.4

1Women who are currently pregnant or experiencing menopause at the time of consultation.2Individuals with confirmed organic lesions causing POI through conventional gynecological examinations, including imaging and secretion examinations.3Participants who have undergone relevant treatments that may potentially influence the observation indicators or treatment outcomes.4Individuals with severe heart, liver, and kidney injuries that may impact normal metabolism.5Participants with combinations of other physiological or pathological conditions that may affect the study's outcome indicators.6Those who withdraw from treatment due to personal reasons.7Participants who fail to strictly adhere to the intervention measures, leading to the inability to collect relevant data or the production of errors in feedback on efficacy and effect indicators.8Individuals experiencing severe adverse reactions or complications during treatment, rendering them unable to continue the intervention.9Participants using drugs that may interfere with the study's treatment plan.10Individuals simultaneously participating in other experiments.11Participants unable to complete the filling of various scales.12Individuals unwilling to be randomly grouped.13Patients with abnormal thyroid function.

Application of these exclusion criteria aims to ensure the suitability of selected participants for the research objectives and reduce potential confounding factors.

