### Sample size

6.4

The calculation of the sample size is derived from the formula comparing two sample rates：$$N=\frac{{\left(Z_{1-\alpha \;}+Z_{1-\beta }\right)}^{2}\left(1+\frac{1}{k}\right)\cdot \sigma^{2}}{{\left(\mu_{T\;}-\mu_{C}-△\right)}^{2}})$$

Here, N represents the required sample size for each group, Pe and *Pc* denote the maximum and minimum effective rates of each group. Based on our retrospective clinical data and previous experimental reports, acupuncture demonstrated a reduction in FSH levels by 20 IU/L, while assuming that the control group reduced FSH levels by 14.5 IU/L. For the study, which is divided into two groups with parameters $\mu_{T\;}$ = 20, $\mu_{C}$ = 14.5, △=3, a test level α = 0.05 and a test efficiency 1-β = 0.9 were considered.

In light of an anticipated 20 % dropout rate, a total of 108 patients will be recruited, ensuring no less than 54 participants in each group. Given the absence of a standardized sample size calculation for transcriptome analysis, the approach aligns with prevalent studies on POI. From the pool of 108 participants, 10 patients in each group (comprising 5 with a decrease of ≥30 % in serum FSH levels after intervention, 5 with a decrease of <30 % in serum FSH levels after intervention, and 10 normal female volunteers in the healthy control group) will be selected for transcriptome analysis.

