### Allocation and blinding

6.5

Participant allocation to either the study or control group will follow a meticulous 1:1 ratio, determined by adherence to predetermined inclusion and exclusion criteria. A prospective cohort study protocol has been devised for individuals diagnosed with POI, stratified by the extent of FSH decline. The exposure factor under investigation is acupuncture treatment, with categorization based on FSH decline exceeding 30 % or less than 30 %, comprising 5 cases each.

In this openly conducted clinical trial, recognition is accorded to the inherent awareness of both patients and involved acupuncturists regarding treatment assignments due to the study's nature. However, to counterbalance potential biases and uphold the scientific rigor of the investigation, specific measures will be instituted to ensure the maintenance of blinding for other pivotal personnel involved in the study.

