### Data collection and management

6.6

Data collection will be conducted at two critical junctures: baseline and postintervention. Trained data collectors, employing case report forms (CRFs), will meticulously record participant information. Specifically, the anxiety and depression levels of participants will be assessed through the administration of the Self-Rating Anxiety Scale (SAS) and Self-Rating Depression Scale (SDS), respectively. Following the CRF-based data collection, the information will be meticulously entered into an electronic database to facilitate streamlined data management.

To bolster accuracy, a dual data entry system will be implemented, involving two data collectors to independently input the data, thereby minimizing errors. Subsequently, the clinical raw data will undergo scrutiny by the project supervisor, who will rectify any identified errors or inconsistencies before proceeding with data export. Once the data's accuracy is affirmed, the database will be securely locked, paving the way for subsequent statistical analyses. Participant identification will be maintained through assigned numbers, and the database will be password-protected to uphold confidentiality.

Oversight of the data will be conducted by the ethical review board of the Shenzhen Maternity and Child Healthcare Hospital. Comprehensive reporting on participant withdrawals and the reasons for withdrawal will be undertaken. In the event of dropouts, modern imputation methods for handling missing data will be employed, ensuring their inclusion in the subsequent analyses.

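### Section 4.4 lists three events that can only occur after treatment starts as exclusion criteria, in conflict with the promise in section 6.6 to impute and include dropouts

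*Protocol article*

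**What the plan says.** The protocol article, section 4.4 (Exclusion criteria), gives one list of 13 items. Most describe a woman's state at entry, such as pregnancy, thyroid function or taking part in another study. Three do not:

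- Criterion 6 covers women who withdraw from treatment for personal reasons.
- Criterion 7 covers women "who fail to strictly adhere to the intervention measures, leading to the inability to collect relevant data or the production of errors in feedback"; the feedback meant is that on the efficacy and effect measures.
- Criterion 8 covers women whose severe reaction or complication during treatment prevents them from continuing.

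The section closes with a statement of purpose: "Application of these exclusion criteria aims to ensure the suitability of selected participants for the research objectives and reduce potential confounding factors".

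Section 6.6 (Data collection and management) deals with the same kind of woman differently: "In the event of dropouts, modern imputation methods for handling missing data will be employed, ensuring their inclusion in the subsequent analyses". It adds: "Comprehensive reporting on participant withdrawals and the reasons for withdrawal will be undertaken".

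Two other places set the context. Section 4.1 describes the randomised comparison: "The allocation ratio is set at 1:1, ensuring an equal distribution of 54 subjects in each group". Section 6.5 acknowledges the "inherent awareness of both patients and involved acupuncturists regarding treatment assignments".

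**The concern.** An exclusion criterion decides who enters a trial. Criteria 6, 7 and 8 cannot do that, because the events they name follow the start of assigned treatment. Applied as written, they exclude a woman who has already been randomised, whereas 6.6 keeps her in the analysis if she drops out. The two rules give different analysis sets for the primary outcome (FSH) and for SAS and SDS.

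Criterion 7 goes further than dropout. It also reaches a woman who has data, if her non-adherence is judged to have made those data erroneous. The article gives no standard for that judgement and does not say who makes it. Section 6.5 promises blinding for other key personnel but does not connect this to criterion 7.

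The arms also ask different things of the women: needling sessions of 30 minutes three times a week (4.6) against daily tablets (4.7). Reasons for withdrawing, not adhering or stopping can plausibly differ between them. If women are then removed for those reasons, the groups compared are no longer the groups that were randomised.

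**Working it through.** **1. The two sections side by side**

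| A randomised woman who… | Under 4.4 | Under 6.6 |
|---|---|---|
| withdraws for personal reasons | excluded (6) | reported with her reason, imputed, included |
| does not adhere, data cannot be collected | excluded (7) | imputed and included if she counts as a dropout |
| does not adhere, data exist but are judged erroneous | excluded (7) | not addressed |
| has a severe reaction and cannot continue | excluded (8) | imputed and included if she counts as a dropout |

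The rules conflict in the first row, and in the second and fourth whenever the woman counts as a dropout. In the third row only 4.4 speaks.

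**2. The plan's own figures (6.4)**

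The plan has 54 women per arm and a 20 % dropout allowance. 0.20 × 54 = 10.8, so about 11 women per arm, leaving about 43. The inflation is coherent: 43 / 0.8 = 53.75, rounded up to 54. The step before it cannot be reproduced, because the article prints no standard deviation. The allowance fits either rule, so it does not settle the conflict.

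The planned effect is stated as "acupuncture demonstrated a reduction in FSH levels by 20 IU/L, while assuming that the control group reduced FSH levels by 14.5 IU/L". The difference is 20 − 14.5 = 5.5 IU/L, and the formula uses △ = 3.

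**3. Shift in one arm's mean if women are removed**

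Let a share p of an arm have an FSH fall that is D IU/L smaller than the mean fall m of the rest. The mean over all randomised women in that arm is m − pD. The mean after removal is m. Removal therefore raises the arm's mean fall by pD.

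Take p = 0.20 from the dropout allowance. The article does not tie that figure to criteria 6 to 8, and it gives no value for D, so both are assumptions.

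| D (IU/L) | 5 | 10 | 15 | 20 |
|---|---|---|---|---|
| Shift pD (IU/L) | 1 | 2 | 3 | 4 |

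With p = 0.10 the shifts are 0.5 to 2 IU/L; with p = 0.30 they are 1.5 to 6 IU/L.

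**4. False-positive rate when the arms do not differ**

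The simulation used 54 women per arm, 5,000 runs per cell and a two-sided t-test at 0.05. Each woman in either arm has a 20 % chance of being a poor responder with deficit D. The assumed standard deviations, 4 and 9, are close to those at which 43 per arm would give 90 % power in the printed one-sided formula, σ = d × √(43/2) / (1.645 + 1.282). For d = 5.5 − 3 = 2.5 this gives 3.96; for d = 5.5 it gives 8.71.

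| SD | D | Poor responders all removed from both arms | All from one arm, half from the other | All from one arm, none from the other |
|---|---|---|---|---|
| 4 | 5 | 5.0 % | 9.9 % | 19.2 % |
| 4 | 10 | 5.0 % | 18.8 % | 48.0 % |
| 9 | 10 | 4.7 % | 8.0 % | 17.6 % |
| 9 | 20 | 5.1 % | 17.3 % | 43.5 % |

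Equal removal of similar women leaves the error rate near 5 %. Unequal removal raises it.

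**The case against.** The strongest reply is that this is a misplaced label in a condensed article. Section 4.4 states its purpose as selecting participants and never mentions the analysis set. The only text on analysing dropouts is 6.6, and that text is inclusive. Analysis populations are commonly left to the full protocol or the analysis plan, so their absence here is no fault. That last point stands. It does not remove the conflict, because both rules are printed in the article and 6.6 does not reach women whose data exist but are judged erroneous.

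Four stronger readings are tempting, and the document does not support them.

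- *Women are removed from the randomised comparison.* A reader might infer this from 4.4, but it is nowhere stated, and 6.6 says otherwise for dropouts. Removal is a possible result of an unresolved conflict.
- *Criterion 11 (cannot complete the scales) is a fourth such event.* It carries no timing. It stands between taking part in other studies and refusing randomisation, and reads at least as naturally as a screening condition.
- *Severe reactions vanish from the safety record.* Section 6.3 requires adverse events from acupuncture to be recorded and serious events to be reported within 24 hours. Criterion 8 does not override that.
- *Criterion 7 selects women by how well they respond.* Its trigger is non-adherence that spoils the data, and it says nothing about the size or direction of the FSH change. The sound objection is that the judgement is loose and could be made by someone who knows the arm.

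The size is also open to challenge, rightly. The deficits are assumed, the removal rates are not in the article, and the imbalance could run either way: section 3 itself says conventional treatments have notable side effects.

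**Conclusion.** The point holds for criteria 6, 7 and 8. They are events after the start of treatment placed in an eligibility list, and they contradict 6.6 on what happens to a randomised woman who drops out. The article does not say which rule prevails.

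If 4.4 were followed, bias would arise to the extent that removal differs between arms. Under the assumptions shown (20 % removed from one arm, deficit of 5 to 20 IU/L), that arm's mean FSH fall is overstated by 1 to 4 IU/L. This is material beside a planned difference of 5.5 and a △ of 3. The figures show sensitivity and are not a forecast. The direction cannot be known from the document, and equal removal of similar women from both arms would not inflate the type I error. The textual conflict depends on none of these assumptions.

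**What to change.** - Keep in 4.4 only conditions that are judged before randomisation.
- Move criteria 6, 7 and 8 out of eligibility and relabel them as treatment-discontinuation or adherence events. Criterion 8 should be reclassified and not simply deleted, so that no rule on stopping treatment changes.
- State that criterion 11 is judged at screening.
- State that every randomised woman stays in her assigned group, has the end-of-treatment FSH, SAS and SDS assessment where she agrees, and is analysed there with the imputation promised in 6.6. This includes women whose adherence is in doubt but who have data.
- Use an adherent subset only as a sensitivity analysis.

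Settle this before the database lock described in 6.6.

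The cost is protocol wording, some end visits after treatment has stopped, and an estimated effect that may be smaller. No larger sample is needed: if the standard deviation is such that 43 per arm gives 90 % power, 54 per arm gives about 95 %, before any allowance for imputation uncertainty or a diluted effect.
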